### Endpoints

The primary endpoints will be **1)** the development of significant renal dysfunction, **2)** the occurrence of any kind of cerebrovascular disease between 0 and 24 weeks (short-term study) from starting the interventions. The significant renal dysfunction will be defined as the conditions that fulfill at least one of the following four criteria; 1. serum Cre level ≥ 1.5 times higher than that at 0 week, 2. eGFR decrease ≥20 ml/min/1.73m^2^ from that at 0 week, 3. proteinuria ≥3.5 g/gCr, 4. new development of urinary stones. The secondary endpoints will be the above-described criteria at 1 and 2 years (long-term study) from starting the interventions, and finding any kind of reno-protective marker associated with alkalinizing agents in both periods of study (Table 3).

**Table 3 Tab3:** Primary and Secondary Endpoints

Endpoints	Period	
Primary	Short-term	1) The development of significant renal dysfunction 1. serum Cre level ≥ 1.5 times higher than that at 0 week 2. eGFR decrease ≥20 ml/min/1.73m^2^ from that at 0 week 3. proteinuria ≥3.5 g/gCr 4. new development of urinary stones 2) The occurrence of any kind of CVD and the death
Secondary	Lon-term	1) The development of significant renal dysfunction 2) The occurrence of any kind of CVD and the death
	Short-term & Lon-term	Reno-protective marker associated with alkalinizing agents in both periods of study, for example, category II (blood tests), categoryII (urine test), urine pH and unknown surrogate biomarkers of early renal damage, including uremic toxins and known metabolites measured by metabolomics.

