**Methods:**

In this single-centered, open-labeled, randomized cohort study, patients with CKD stages G2, G3a and G3b, who visited and were treated at Tohoku University Hospital during the enrollment period were registered. We administered sodium bicarbonate or sodium-potassium citrate as the oral alkalinizing agents. A total of 150 patients with CKD will be randomly allocated into the following three groups: sodium bicarbonate, sodium-potassium citrate and standard therapy group without any alkalinizing agents. The data of performance status, venous blood test, spot urine test, venous blood-gas test, electrocardiogram, renal arterial ultrasonography and chest X-ray will be collected at 0, 6, 12 and 24 weeks (short-term study) from starting the interventions. These data will be also collected at 1 and 2 years (long-term study). The samples of plasma and serum and early-morning urine at every visit will be acquired for the analysis of renal function and surrogate uremic biomarkers.

The recruitment for this cohort study terminated in March, 2018, and the follow-up period for all the enrolled subjects will be terminated in December, 2020. The primary endpoint will be the development of originally-defined significant renal dysfunction or the occurrence of any cerebrovascular disease in the short-term study. The secondary endpoint will be the same endpoints as in the long-term study, or the patients with significant changes in the suggested the surrogate biomarkers.

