## Background

Chronic kidney disease (CKD) is a chronic progressive disease related to eating habits and lifestyle [1–3]. These days, the increment of end-stage kidney disease (ESKD) is one of the biggest problems in the management of CKD patients [4]. If the patients with CKD are not properly treated, the disease may lead to cardiovascular events as well as ESKD and renal death [5, 6]. The treatment to ameliorate tubulo-interstitial dysfunction in the progression of CKD is important for preventing the final common pathway leading to ESKD [7, 8], which is yet to be verified by clinical research.

Generally, renal dysfunction may lead to metabolic acidosis and hyperkalemia, both derived from the accumulation of acidic metabolic wastes produced in daily life [9–11]. The acidic metabolic compounds, called uremic toxins (UTs), are the substances that primarily cause the aciduria [12, 13]. The accumulation of UTs is more common in CKD patients than in healthy individuals because of the disturbed urinary excretion from the damaged kidneys [14]. Some types of UTs are known to stimulate the ROS production, which may lead to further renal tubule-interstitial dysfunction [15, 16]. Physiological acidification in renal tubules is not harmful itself; however, we previously reported that a stronger acid condition in renal tubules could result in an increased production of reactive oxidative stress (ROS), which could be aggravated by albuminuria [17]. In this previous study with a CKD animal model, an oral alkalinizing agent also improved aciduria by neutralizing renal intratubular pH and alleviating the latent metabolic acidosis.

In several past reports, treatments with some alkalinizing agents (sodium bicarbonate and sodium citrate) ameliorated renal damage in CKD patients with eGFR < 60 ml/min/1.73m^2^ [18–20]. In addition, intake of fruits and vegetables also ameliorated the renal dysfunction and high blood pressure [21]. Oral alkalinizing agents are also suggested to be useful for prolonging the initiation of hemodialysis by some unknown mechanisms, but this possible effect is still to be scientifically established.

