### Collected variables

At the time of registration, written informed consent is acquired from all the enrolled patients. At this time, the following information as to the patient’s background are also collected: birthdate, sex, past medical history, complications, medication history, allergic history, smoking history, amount of alcohol intake, body weight and height.

The routine physical examinations, medication usage, and occurrence of adverse events are confirmed at every check-up in both the short-term and the long-term assessments.

Other data concerning the quality of life (QOL), laboratory test, chest X-ray, and physiological studies are confirmed at the set periods shown in Table 1. In detail, cardiac-thoracic ratio and presence of congestion for chest XRs, severe arrhythmia, angina pectoris and acute myocardial infarction for ECG and intrarenal blood flow and renal size for renal US. The QOL was assessed by using the SF-8™ Health Survey (Standard, Japanese version) by QualityMetric Incorporation and Shunichi Fukuhara (iHope international) [24]. The details of each blood test category and urine test category are listed in Table 2.

**Table 1 Tab1:** Items and timing of laboratory and physiological examinations for short-term and long-term assessments

	Short-term				Long-term	
	0 wk	6 wks	12 wks	24 wks	1 year	2 year
QOL (SF-8™)	○	–	–	○	–	–
Blood test						
Category I	○	○	○	○	○	○
Category II	○	–	–	○	△	△
Urine test						
Category I	○	○	○	○	○	○
Category II	○	○	○	○	△	△
ECG	○	–	–	○	○	○
CAVI, ABI	○	–	–	○	○	○
Renal US	○	–	–	○	○	○
Chest X-ray	○	–	–	○	○	○

Details of the categories I and II of both blood and urine tests are listed in the following Table 2. The circles show that the examinations will be performed at each time without exceptions. The triangles show that the examinations will be performed if the measured values in the short-term period showed abnormality and their follow-up is suggested to be desirable

**Table 2 Tab2:** Details of categories I and II of both blood and urine tests

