### Analysis

The measured variables in the three groups will be compared by the analysis of variance (ANOVA), followed by the Bonferroni’s post-hoc comparisons. If the variables show apparent non-normal distributions, Kruskal-Wallis test will be applied as a non-parametric test. Because of the simultaneous multiple comparisons, *p*-value < 0.01 will be regarded as statistically significant. The chronological change of each variable in each group will be also evaluated. Values in each pair will be compared by the paired Student’s t-test. If the variables show apparent non-normal distributions, Wilcoxon’s rank sum test will be adopted. Comparisons of outcome with dichotomous data (i.e. frequency) between the groups will be performed by either of chi-squared test or Fisher’s exact test, based on the achieved frequency in each cell. Lastly, to clarify the correlations between urine pH, both for the early-morning urine and spot urine, and serum creatinine levels, Spearman’s correlation coefficient for each pair will be calculated, followed by the test of no correlation.

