## Discussion

Recruitment to this cohort study terminated in March, 2018, and the follow-up period for all the enrolled subjects will be terminated in December, 2020.

We will seek for new therapeutic strategies using oral alkalinizing agents for the early stage CKD patients in this CKOALA study. Based on the previous study that showed the reno-protective effects of the oral sodium bicarbonate in the animal CKD model [17], we hypothesized that administration of oral alkalinizing agents for the patients with mild and moderate stages of CKD would delay the development of ESKD. This cohort study will confirm the reported benefits of oral alkalinizing agents for suppressing CKD progression in actual human cases.

In addition to the expectation that this study will confirm the therapeutic effects of oral alkalinizing agents for CKD patients, it would also clarify the relationship between the urine pH and the chronic renal damage. Because the oral alkalinizing agents have been suggested to only alkalize the urine without changing serum pH, if the reno-protective effects of oral alkalinizing agents are confirmed, it will strongly suggest that aciduria is a definite risk factor to promote the renal damage in CKD patients.

One of the strengths of this study is that it will be conducted in a single center, which will enable us to exclude the risks of biases based on the differences between facilities and examiners. Meanwhile, there are some limitations. First, the number of enrolled subjects may remain low. If the results become negative due to inadequate sample size, we may extend the study period or plan additional randomized multi-center cohort study to achieve an adequate sample size. Another limitation is that this study will be an open-label trial. However, because the endpoints of this study are comprised of objectively measured serum and urine biomarkers that could not be affected by the preconceptions, biases based on the open-label style of this study to the given endpoints are not likely. Lastly, as for the patients’ compliance to the medications, we will interview the intake habit at all the occasions of their hospital visits.

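### The Endpoints text and abstract define the second primary component as cerebrovascular disease; Table 3 defines it as an unexpanded CVD plus death, and nothing says which governs

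*Protocol article*

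**What the plan says.** All references are to the protocol article.

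- **Endpoints, text.** The second primary endpoint is "the occurrence of any kind of cerebrovascular disease between 0 and 24 weeks (short-term study". Death is not mentioned.
- **Abstract, Methods.** One primary endpoint, formed of renal dysfunction *or* "the occurrence of any cerebrovascular disease in the short-term study". Death is not mentioned.
- **Table 3**, cited by the Endpoints text. The second component is "The occurrence of any kind of CVD and the death", listed once for the short-term primary endpoint and again for the long-term secondary endpoint.
- **Endpoints, long-term.** "The secondary endpoints will be the above-described criteria at 1 and 2 years (long-term study) from starting the interventions", so the later endpoint takes over whatever the short-term definition is.
- **Abbreviations.** CVD is not listed, and it is not spelled out elsewhere.
- **Collected variables.** The items recorded include "severe arrhythmia, angina pectoris and acute myocardial infarction for ECG".
- **Background.** Of untreated CKD it says that "the disease may lead to cardiovascular events as well as ESKD and renal death".
- **Censoring criteria.** Adverse events such as worsening cardiac, hepatic or renal symptoms are a reason for censoring, and data of censored subjects are to be excluded.
- **Analysis.** Comparisons of dichotomous outcomes "will be performed by either of chi-squared test or Fisher’s exact test, based on the achieved frequency in each cell".
- **Discussion.** Open-label bias is considered unlikely because "the endpoints of this study are comprised of objectively measured serum and urine biomarkers".

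**The concern.** A primary endpoint has to settle, for each patient, whether an event occurred. Here it does not settle this for a patient who dies by week 24, and it may not for one who has a cardiac event. The long-term secondary endpoint inherits the same gap at 1 and 2 years.

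The timing adds to the problem. The trial is open-label, recruitment closed in March 2018, and the article appeared in April 2020. If treatment began soon after enrolment, every patient had passed week 24 before publication. If the definition is settled only now, it can be settled with outcomes and allocation known.

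**Working it through.** **Step 1: classify the same patient under each version.** Take a patient who meets none of the four renal criteria by week 24. The word *and* in Table 3 is read as listing two kinds of event, not as requiring both in one patient.

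| What happens by week 24 | Endpoints text and abstract | Table 3, CVD = cerebrovascular | Table 3, CVD = cardiovascular |
|---|---|---|---|
| Death without cerebrovascular disease | no event | event | event |
| Myocardial infarction, survives | no event | no event | event |

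The first row differs between text and table however CVD is read, so that is a contradiction. The second row differs only under the cardiovascular reading, so that is an ambiguity.

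**Step 2: add the Censoring criteria.** An infarction could also be handled as an adverse event with worsening cardiac symptoms, and the patient's data excluded. The same patient could then be an event, a non-event or absent from the analysis. Worsening renal symptoms are on the same list, so the overlap may reach the renal component too.

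**Step 3: structure.** The abstract joins the renal and vascular parts with *or* under a single primary endpoint: one event indicator and one comparison. The Endpoints text numbers them as two primary endpoints: two indicators and two comparisons. The event counts and the multiplicity differ.

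**Step 4: how far one event can move the result.** The plan states no figure to reproduce here, and no expected rate of deaths or vascular events. The counts below are assumed, to show sensitivity only. Inputs: 50 per group (Sample size calculation); Fisher's exact test, two-sided by assumption; thresholds of 0.05 (Sample size calculation) and 0.01 (Analysis). Each p-value is for the 2×2 table with rows (a, 50 − a) and (b, 50 − b).

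| Events a v b | p | One more event in the second group | p | Threshold crossed |
|---|---|---|---|---|
| 0 v 5 | 0.056 | 0 v 6 | 0.027 | 0.05 |
| 1 v 7 | 0.059 | 1 v 8 | 0.031 | 0.05 |
| 0 v 7 | 0.0125 | 0 v 8 | 0.0058 | 0.01 |
| 1 v 9 | 0.016 | 1 v 10 | 0.008 | 0.01 |

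**Step 5: the same check away from the threshold.** The only rates in the document are 5% and 30%, given for ESKD and not for this endpoint. They imply 0.05 × 50 = 2.5 and 0.30 × 50 = 15 events.

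- 2 v 15: p = 0.0009. 3 v 15: p = 0.0033.
- One event fewer in the higher group, 3 v 14: p = 0.0064.
- One event more in the lower group, 4 v 15: p = 0.0095.

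All four stay below both 0.05 and 0.01.

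**The case against.** The strongest reply is that CVD in Table 3 merely abbreviates the phrase in the text that cites the table, with the abstract in support. The Background sentence on cardiovascular events is general, and the ECG findings are listed among items collected, beside chest X-ray and renal ultrasound, not as endpoints. This reply stands for cardiac events: it leaves an ambiguity, not a contradiction. It does not help with death, which Table 3 adds and the other two places omit.

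A reader might infer from the first table of p-values that reclassifying one infarction or death reverses the trial's conclusion. The documents do not support that. Those pairs were chosen at the threshold, where any test changes sides, and at the stated 5% v 30% one event changes nothing.

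A reader might also infer that, if death is not an event, patients who die drop out of the renal endpoint. The Censoring criteria do not list death, and no section says how deaths enter the renal component. Such handling is commonly left to a full protocol or SAP that is not shown.

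On the Discussion's open-label argument, three of the four renal criteria are laboratory values. The sentence is incomplete rather than baseless, and it has no bearing on which vascular events count.

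**Conclusion.** The point holds as an internal inconsistency in the primary endpoint. It is certain for death, which is a primary event in Table 3 and not in the Endpoints text or abstract. For cardiac events it is an unresolved ambiguity that rests on one unexpanded abbreviation. The split between a composite and two numbered endpoints is a further inconsistency in the same definition.

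The effect on the result cannot be sized, because no rate of deaths or vascular events is given. One reclassified event could change a borderline result with 50 per group; it would not change one near 5% v 30%. This rests on full groups of 50, two-sided Fisher tests between two groups and illustrative counts. The inconsistency itself rests on none of these. It needs correcting because the plan, followed as written, does not determine who has a primary event.

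**What to change.** Before the analysis:

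1. Use one definition in the abstract, the Endpoints text and Table 3: the one originally registered or approved. Disclose any departure from it, with its date and whether outcomes were known. Adopting a broader composite now, for instance by adding cardiac events or all-cause death, would itself be a late choice in an open-label trial unless it was already the approved definition.
2. Expand CVD, and state whether death counts and from which causes. Apply the same wording to the long-term endpoint.
3. State whether the renal and vascular parts form one composite or separate primary endpoints.
4. Reconcile the Censoring criteria with the endpoint, so that a patient with an endpoint event is not excluded from the analysis because of it.
5. Report each component separately.
6. As a minor matter, limit the Discussion's statement about objective serum and urine biomarkers to the laboratory components. New urinary stones and vascular disease are clinical diagnoses, and death is not a biomarker.

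The cost is wording, plus disclosure of any change. No new data are needed. The registry record was not available for this review, so nothing here implies that it needs changing.

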### Eligibility criteria for participants

The patients, 20 to 80 years of age with CKD stages G2, G3a and G3b who were treated at Tohoku University Hospital between March, 2014 and March, 2018, will be eligible for this study. As for the exclusion criteria, patients who were administered with any medications or drinks that could have possible alkalinizing effects, or patients with tolvaptan within 30 days prior to the registration will be excluded. In addition, patients with renal hypouricemia, hyperkalemia, diabetes insipidus, hypernatremia with unknown origins, morning urinary pH higher than 6.8, or serious complications of heart disease or liver disease will also be excluded. Patients with hyperuricemia, morning aciduria, or metabolic acidosis will not be excluded.

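### The proteinuria criterion of the primary endpoint has no week-0 or new-onset reference, so patients who enter at or above 3.5 g/gCr and stay there can count as events without worsening

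*Protocol article*

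**What the plan says.** Under Endpoints, the first primary endpoint is "the development of significant renal dysfunction" in the window "between 0 and 24 weeks (short-term study) from starting the interventions". A patient has it on meeting the condition to "fulfill at least one of the following four criteria":

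- Criterion 1: "serum Cre level ≥ 1.5 times higher than that at 0 week"
- Criterion 2: "eGFR decrease ≥20 ml/min/1.73m^2^ from that at 0 week"
- Criteria 3 and 4: "3. proteinuria ≥3.5 g/gCr, 4. new development of urinary stones"

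Table 3 repeats the list unchanged. The secondary endpoint applies the same criteria at 1 and 2 years.

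Eligibility is by age and GFR stage (G2, G3a, G3b). The exclusion list covers alkalinizing products, tolvaptan and several conditions, and ends with "morning urinary pH higher than 6.8, or serious complications of heart disease or liver disease will also be excluded". It contains no limit on proteinuria or albuminuria. The randomization strata (Overview of study design) are age, sex, diabetes and eGFR. Urine protein and creatinine belong to urine Category I (Table 2), which Table 1 schedules for everyone at weeks 0, 6, 12 and 24 and at 1 and 2 years.

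**The concern.** Three of the four criteria describe something that happens after the start: a rise in creatinine, a fall in eGFR, a new stone. Criterion 3 describes a state that a patient may already be in at randomization. Because one criterion is enough, such a patient can enter the primary event count on a characteristic that predates the intervention.

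If these patients stay above the level, they add the same expected number of events to every arm. That narrows the difference between arms, pulls the risk ratio towards 1 and lowers power. It also makes the result harder to interpret, since an event need not mean progression. Two analysts could count different primary events from the same data, depending on how much weight they give to the word 'development'. In an open-label trial, that choice should not be left until outcomes are known.

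**Working it through.** **1. The definition.** Setting the four criteria side by side:

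| Criterion | Reference to week 0 | Requires onset |
|---|---|---|
| 1 creatinine | yes | through the change |
| 2 eGFR | yes | through the change |
| 3 proteinuria | no | no |
| 4 stones | not needed | yes ('new') |

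No eligibility rule removes patients who already meet criterion 3. The population is called mild, but it is selected by GFR stage, which does not bound proteinuria. Patients with diabetes are enrolled, since diabetes is a stratification factor.

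**2. The plan's own sample size.** Inputs (Sample size calculation): 5% and 30%, alpha 0.05, power 80%, 50 per group. With p̄ = (0.05 + 0.30)/2 = 0.175 and a two-sided test,

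n = [1.960 × √(2 × 0.175 × 0.825) + 0.842 × √(0.05 × 0.95 + 0.30 × 0.70)]² / 0.25² ≈ 35.1,

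so 36 per arm, or 43 with continuity correction. The stated 50 is not reproduced; an unstated allowance for dropout or multiplicity could explain it. That is a separate matter, and nothing below depends on it except that n = 50 is used.

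**3. Dilution.** Let q be the share already at or above 3.5 g/gCr at week 0. The document does not give q, so it is an assumption. In the worst case every such patient is an event in either arm, and the observed rate is

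p′ = q + (1 − q)p.

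For q = 5%: 0.05 + 0.95 × 0.05 = 9.75% and 0.05 + 0.95 × 0.30 = 33.5%. The risk ratio moves from 0.05/0.30 = 0.17 to 0.0975/0.335 = 0.29, and the difference from 25 to 23.75 points. Five per cent of 50 is 2.5 patients per arm.

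Two-sided power with 50 per arm at alpha 0.05, by exact enumeration of both binomials (Fisher's test, then chi-squared without correction), with the normal approximation as a check:

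| q | Rates compared | Risk ratio | Fisher to chi-squared | Normal approximation |
|---|---|---|---|---|
| 0% | 5% vs 30% | 0.17 | 90-95% | 92.0% |
| 3% | 7.85% vs 32.1% | 0.24 | 83-89% | 87.0% |
| 5% | 9.75% vs 33.5% | 0.29 | 79-85% | 83.3% |
| 10% | 14.5% vs 37% | 0.39 | 68-75% | 73.7% |

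At the p < 0.01 threshold named under Analysis, the Fisher to chi-squared range is 75-82% at q = 0, 57-65% at 5% and 43-51% at 10%.

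**4. False positives.** With no treatment effect and both arms at 9.75% or 14.5%, the exact rejection rate at nominal 5% is 1.8-2.3% for Fisher and 5.0-5.5% for chi-squared. The small excess over 5% is the usual behaviour of the uncorrected chi-squared test with discrete data.

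**The case against.** The strongest counter-argument is the heading word 'development': someone above the level at week 0 has arguably not developed anything. This stands as a source of ambiguity, but it does not settle the matter. The term is then explicitly defined by the four criteria, the window opens at week 0, and if the heading already implied onset, 'new' in criterion 4 would be redundant.

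A second argument is that the article condenses a fuller protocol, which may handle such patients. That is possible. However, the article gives the endpoint definition in full, twice, and qualifies the other three criteria. If a rule exists elsewhere, the published definition should match it.

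Three stronger readings are tempting, and the document does not support them:

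- A reader might infer that every patient above the level at entry is an event whatever the treatment. That is so only if the week-0 value itself counts or proteinuria stays at or above 3.5 g/gCr. If only later visits count, a patient who falls below the level by week 6 and stays there is not an event.
- A reader might infer that chance imbalance in these patients, who are not stratified for, could produce a spurious finding. Imbalance is common: under simple binomial allocation, two arms differ by 3 or more such patients with probability about 24% at q = 5% and 40% at q = 10%. But the test's error rate already covers chance imbalance, as step 4 of the working shows. Leaving proteinuria out of the strata is not an error in itself.
- A reader might take the power figures as a forecast. They rest on an assumed share, which could be near zero, and on 5% and 30%, which the article gives as ESKD incidences and not as 24-week rates of this composite.

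**Conclusion.** The point holds as a defect of definition. Criterion 3 is the only one of the four without a baseline or onset condition, nothing in eligibility closes the gap, and the long-term endpoint inherits it. This conclusion needs no assumption about numbers.

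The consequence is diluted effect and lost power, with no inflation of the type I error. Its size cannot be fixed from the document. In the worst case, where every patient above the level at entry stays above it, a 5% share leaves power at 79-85%, about the planned 80%. A 10% share takes it to 68-75%, clearly below plan. Confidence is high on the wording and low on the impact.

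**What to change.** Reword criterion 3 in the Endpoints section and Table 3 along these lines: *proteinuria ≥3.5 g/gCr after week 0 in a patient with <3.5 g/gCr at 0 week*. State that patients already at or above the level at week 0 remain in the analysis and are assessed on criteria 1, 2 and 4 and on the vascular and death component, so that the randomized groups stay intact. Apply the same wording at 1 and 2 years. Settle the rule without reference to outcome data; it needs only week-0 values.

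The cost is one sentence and no new measurements, since urine protein and creatinine are scheduled at week 0 for everyone. There are two downsides. Somewhat fewer events will be counted, and worsening proteinuria in patients already above the level will no longer be captured by this criterion. A move just across the threshold, for example from 3.4 to 3.5 g/gCr, would still count as an event. If the sponsor wants to capture worsening or avoid such marginal crossings, a criterion based on change from week 0 is an alternative, also to be fixed in advance.

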**Category I (urine test)**	
Creatinine, protein, albumin, pH, Na, K, Cl, urobilinogen, bilirubin, ketone body, occult blood, urinary sediments	

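### Proteinuria is a named endpoint only as an absolute 3.5 g/gCr cut with no week-0 reference; its between-arm change, measured at all six visits, is left to generic unadjusted tests

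*Protocol article*

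**What the plan says.** In the protocol article, Endpoints section and Table 3, significant renal dysfunction means meeting at least one of four criteria. The third is "proteinuria ≥3.5 g/gCr". It has no baseline reference, whereas the creatinine criterion and the eGFR criterion ("eGFR decrease ≥20 ml/min/1.73m^2^ from that at 0 week") are both tied to week 0. The long-term endpoint reuses the set: "The secondary endpoints will be the above-described criteria at 1 and 2 years (long-term study) from starting the interventions".

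Table 2 places "Creatinine, protein, albumin, pH, Na, K, Cl" in urine Category I. Table 1 schedules Category I urine at 0, 6, 12 and 24 weeks and at 1 and 2 years, without exceptions. Category II urine is complete to 24 weeks; at 1 and 2 years it is done only where short-term values were abnormal and follow-up seems desirable.

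The other secondary endpoint is "finding any kind of reno-protective marker associated with alkalinizing agents in both periods of study". Table 3 illustrates it: "for example, category II (blood tests), categoryII (urine test), urine pH and unknown surrogate biomarkers of early renal damage". Urine protein and albumin are not among the examples.

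The Analysis section compares the measured variables across the three groups by ANOVA or Kruskal-Wallis, with p<0.01 as the significance level. It evaluates change over time in each group with paired tests. Binary outcomes go to chi-squared or Fisher's exact test.

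**The concern.** Objective 1 is renal protection in mild to moderate CKD. Urinary protein is a graded damage measure with complete scheduled data over both study periods, yet the only form in which the plan names it as an endpoint is one high absolute cut. Most of the information in a graded reduction is lost at such a cut. The Background also brings albuminuria into the trial's rationale, saying of acid-driven oxidative stress "which could be aggravated by albuminuria".

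The cut has a second weakness. Without a week-0 reference, and with no upper proteinuria limit in the eligibility criteria, a patient who enters at or above 3.5 g/gCr could be counted as having developed renal dysfunction without any deterioration.

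At stake is whether a real, moderate effect of alkali on proteinuria would be seen, and whether a positive result would count as a named endpoint or as one unranked test among dozens of analytes.

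**Working it through.** **Inputs from the documents.** 50 patients per arm; p<0.01 in the Analysis section and 0.05 in the sample-size section; the 3.5 g/gCr cut. The plan gives no figure for proteinuria to reproduce: its sample size is built on ESKD rates and is used here only for n.

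**Assumed inputs (none are in the documents).** Log-normal urine protein/creatinine with baseline median m = 0.15–1.5 g/gCr; SD of log baseline s = 1.0–1.3; SD of within-patient log change w = 0.5–0.7; true reduction r = 30–50%; one follow-up visit.

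**Step 1: the cut, read literally (at or above 3.5 at the visit).** The control proportion is 1 − Φ[ln(3.5/m)/√(s²+w²)]; for alkali, m becomes m(1−r). Example with m = 0.5, s = 1.3, w = 0.7, r = 50%:

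- √(1.69+0.49) = 1.476
- control: ln 7/1.476 = 1.946/1.476 = 1.318, giving 9.4% (4.7 of 50)
- alkali: ln 14/1.476 = 2.639/1.476 = 1.787, giving 3.7% (about 1.9 of 50)
- exact Fisher power: 8% at 0.05 and 2% at 0.01

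Over the grid:

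| Baseline median (g/gCr) | Controls at or above 3.5 | Power at 0.05 | Power at 0.01 | Power at 0.05, new crossings only |
|---|---|---|---|---|
| 0.15–0.5 | 0.2–9% | 0–8% | 0–2% | at most 1.4% |
| 1.0 | 13–20% | 7–22% | 2–9% | at most 10% |
| 1.5 | 22–28% | 10–39% | 3–19% | at most 17% |

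**Step 2: log change, one alkali arm against control.** Power = Φ[|ln(1−r)|/(w√(2/50)) − z], with √(2/50) = 0.2. For r = 30%, |ln 0.7| = 0.357.

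- w = 0.5: 0.357/0.10 = 3.57; 3.57 − 1.96 = 1.61, power 95% at 0.05; 3.57 − 2.576 = 0.99, power 84% at 0.01
- w = 0.7: 0.357/0.14 = 2.55; 2.55 − 1.96 = 0.59, power 72% at 0.05; 2.55 − 2.576 = −0.03, power 49% at 0.01

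For r = 50% the power is 99% or more in every case.

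**Step 3: the fallback in the Analysis section.** Simulation with m = 0.5, s = 1.2, w = 0.5–0.7, a 30% reduction in both alkali arms and 50 per arm, at p<0.01:

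- Kruskal-Wallis on week-24 levels, three arms: about 8–9%
- 3.5 g/gCr cut, one alkali arm against control: under 1%
- log value adjusted for week 0, one alkali arm against control: about 46–81%
- like for like with the first line, three-arm ANOVA on log change: about 50–87%

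For a 50% reduction, Kruskal-Wallis on levels reaches 46–53%, and change exceeds 99%.

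The gap comes from between-patient spread. Week-24 log levels have SD √(1.44+0.25) = 1.30 to √(1.44+0.49) = 1.39, against 0.5–0.7 for change. These inputs imply a correlation between week 0 and week 24 of 1.2/1.30 = 0.92 to 1.2/1.39 = 0.86. A lower correlation would narrow the gap.

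**The case against.** The strongest reply is that proteinuria is not confined to the cut. The marker endpoint admits any kind of marker, its list is illustrative, and urine protein and albumin are measured variables that the Analysis section covers. That stands: a reader might infer that a proteinuria effect has nowhere else to appear, and the documents do not support this. What the reply does not supply is a named endpoint or a between-arm comparison of change. As written, groups are compared on the variables themselves and change is assessed within groups, and Step 3 shows what that costs.

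A reader might also infer that a large effect would almost never register at the cut. That depends on baseline proteinuria, which is not given. It fits low baselines; at medians of 1.0–1.5 g/gCr the power is poor but not negligible. Nor do the documents say that only a new crossing counts, so the new-crossings column above is one possible reading.

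Three further points stand as limits. The cut is one of four components and is never tested alone, so its power is not that of the composite. The endpoint window also includes weeks 6 and 12, which the single-visit calculation leaves out. The Background presents albuminuria as an aggravating factor, not as the outcome of alkali, and Objective 3 seeks new markers, so the case rests on Objective 1.

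It can also be said that model details belong in an analysis plan that is not shown. That holds for the model, but Table 3 does set out the endpoints, and this one is not there.

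**Conclusion.** The point holds as a worthwhile, inexpensive improvement. A severe-event threshold inside a composite is a legitimate choice. The weakness is that it is the only named proteinuria endpoint, that it lacks the week-0 reference its neighbouring criteria have, and that the generic analysis does not recover what the cut discards.

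The direction is stable over the assumed range at 0.05: the cut's best case (39%) is below the worst case for log change (72%). The exact sizes are not established by the documents. They rest on the assumed baseline distribution, the within-patient variability and a 30–50% reduction.

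**What to change.** Add one secondary endpoint to Table 3: the between-arm difference, each alkali arm against standard therapy, in log urine protein/creatinine and log albumin/creatinine, at 24 weeks and over all visits. Adjust for the week-0 log value and report a ratio of geometric means with its confidence interval. Use whichever sample, early-morning or spot, was consistently assayed; the Overview of study design says both are collected, and Table 2 does not say which serves for Category I protein and albumin.

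Label the endpoint as added after recruitment closed. Recruitment ended in March 2018 and the article appeared in April 2020, so in this open-label trial it cannot be presented as specified from the outset.

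Separately, state how patients already at or above 3.5 g/gCr at week 0 are counted under criterion 3.

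The cost is one endpoint line, one model and one sentence. The measurements are already scheduled at every visit. The downside is one more secondary analysis (two ratios, two contrasts each) to account for in the multiplicity.
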